### Study Setting

This study will be conducted at the Department of Obstetrics and Gynecology, Faculty of Medicine, Siriraj Hospital, Mahidol University, Bangkok, Thailand. Siriraj Hospital is the largest university-based tertiary care hospital in Thailand, with approximately 4000 deliveries per year. Routine GDM screening is offered to all pregnant women, and those with GDM are managed by a specialized care team, including an obstetrician, certified diabetes educator nurses, and endocrinologists. All women with GDM receive counseling regarding nutritional therapy, behavioral modification, and glycemic monitoring. Metformin has been incorporated into the guideline as an optional pharmacological therapy, as an alternative to insulin.

### GDM Diagnosis and Management

According to current institutional guidelines, GDM screening and diagnosis are offered to all pregnant women at the first antenatal care visit and repeated at 24 to 28 weeks of gestation if the initial screening results are normal. A 50-g glucose challenge test is used as a screening test with a 140 mg/dL cutoff value, and a 100-g oral glucose tolerance test is used for diagnosis using the Carpenter and Coustan criteria (≥2 abnormal values of 95, 180, 155, 140 mg/dL at 0, 1, 2, and 3 h). The current prevalence of GDM in the institution is approximately 15% to 20% of pregnant women.

After diagnosis, nutritional counseling and knowledge on behavioral modification are provided by certified diabetes educators. A glucometer is encouraged and offered for self-monitoring blood glucose (SMBG), but its use is based on women’s preference. FPG or 2-hour PPG, or both, are used for evaluation of glycemic control during follow-up. Glycemic targets are set at FPG <95 mg/dL and 2-hour PPG <120 mg/dL in >80% of the total SMBG test results.

If glycemic targets are not met at any time during pregnancy, repeat nutritional and behavioral counseling is offered. The women are reevaluated every 1 to 2 weeks. If adequate glycemic control is still not achieved within 4 weeks, pharmacological treatment will be initiated. In addition to insulin therapy, metformin will be offered as an alternative medication. The decision on choices of pharmacological therapy is based on the physician’s discretion and the woman’s preference.

### Eligibility Criteria

Eligible cases are pregnant women diagnosed with GDM who meet the inclusion and exclusion criteria, as described in Textbox 1.

Inclusion and exclusion criteria.
**Inclusion criteria**
Aged ≥18 ySingleton pregnancyDiagnosed with gestational diabetes mellitus, according to institutional guidelines (50-g glucose challenge test followed by 100-g oral glucose tolerance test using the Carpenter and Coustan criteria)Do not achieve glycemic target after nutritional and behavioral counseling (fasting plasma glucose ≥95 mg/dL or 2-hour postprandial glucose ≥120 mg/dL in >20% of total self-monitoring blood glucose test results)
**Exclusion criteria**
Definite or suspected pregestational diabetes mellitusFetal congenital anomalies or deathsSuspected fetal growth restriction (as metformin is advised to be used with caution in those with fetal growth restriction)Currently using metformin or other antihyperglycemic treatment regardless of indicationContraindicated for metformin use

### Interventions

After initial screening and acquiring informed consent, the women will be randomly assigned to 2 groups—the intervention group or the control group.

For the intervention group, metformin PR will be provided to the participants, starting with 750 mg daily (1 tablet of metformin PR 750 mg). Follow-up is scheduled every 2 weeks for 6 weeks. Dosage adjustment will be made at each visit, depending on the results of glycemic control in a step-up protocol, that is, 750, 1000, 1500, and 2000 mg. The maximum dosage of metformin PR is 2000 mg per day. For dosage adjustment, 1 tablet of metformin PR 1000 mg will be used for a dosage of 1000 mg per day, 2 tablets of metformin PR 750 mg will be used for a dosage of 1500 mg per day, and 2 tablets of metformin PR 1000 mg will be used for a dosage of 2000 mg per day.

Pregnant women who are in the control group will receive 1 tablet of a placebo and will be scheduled for follow-up every 2 weeks for 6 weeks.

In addition to standard antenatal care according to institutional guidelines, pregnant women in both groups will receive individualized counseling on nutrition and behavioral modifications for glycemic control at every follow-up visit.

All participants are encouraged to adhere to the medication provided. A specific phone number will be provided to participants to receive an answer if they have any questions about the medications. Participants will be contacted every 2 days via a telephone call, SMS, or other online platforms to ensure medication adherence. Pill count will be performed at every visit, and additional encouragement will be provided. All participants are advised to avoid using other antidiabetic medications and other herbal products during the study period.

At the end of the study period of 6 weeks, glycemic control will be evaluated thoroughly, and appropriate treatment will be provided. Either the previous treatment will be continued or a new treatment will be initiated, after consultation with an endocrinologist, as appropriate. Standard antenatal care will also be provided until delivery. Treatment failure is defined as inadequate glycemic control after 2000 mg of metformin PR. In such a situation, insulin therapy is initiated.

If any of the conditions in the exclusion criteria are detected after enrollment, such as congenital anomalies, randomization concealment will be revealed and considered as a dropout, and these participants will not be included in the analysis. The pregnant woman will be thoroughly evaluated by the obstetrician team to provide appropriate management.

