## Methods

### Study Design

The study is designed as a randomized, double-blind, placebo-controlled trial and registered at the Thai Clinical Trial Registry (TCTR20250525007). Eligible participants will be randomly assigned in a 1:1 ratio to receive either metformin PR or a placebo. Each participant will be followed up every 2 weeks for glycemic control evaluation and dosage adjustment for 6 weeks.

According to the institutional practice guidelines, every woman with GDM will receive counseling by certified diabetes educator nurses and will be scheduled for follow-up every 2 weeks for glycemic control evaluation. If the glycemic target is not achieved after 6 weeks of intensive nutritional therapy, additional pharmacological treatment will be initiated. Therefore, this study will evaluate the primary outcome of glycemic control at 6 weeks after randomization.

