### Outcomes

The primary outcome of this study is the rate of achievement of optimal glycemic control within 6 weeks, which is defined as FPG <95 mg/dL or 2-hour PPG <120 mg/dL in >80% of total SMBG test results.

The secondary outcomes include time to achievement of optimal glycemic control, rate of insulin therapy, and rate of side effects. Treatment failure is defined as inadequate glycemic control after 2000 mg of metformin PR. In this situation, insulin therapy is initiated. Side effects will be evaluated by interviewing the participants at each visit and by additional contact via a telephone call, SMS, or other online platforms.

The participant timeline is displayed in Figure 1.

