#### Blinding

All participants will be blinded to the treatment received. Placebos will be prepared by a pharmacist to resemble metformin PR in shape, size, and color. All caring obstetricians will be blinded to the treatment and make decisions on dosage adjustment or initiation of insulin therapy at their discretion. Glycemic control will be blindly assessed by the investigators without knowing the group to which the participants are assigned.

In case of withdrawal or termination of the study protocol, such as the occurrence of severe adverse events or noncompliance, the treatment will be unblinded. Further individualized management will be provided as appropriate. In addition, emergency unblinding will be performed if the participants need to be evaluated or treated for medical or obstetric conditions other than GDM.

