#### Adverse Event Reporting and Harms

Any adverse events will be evaluated by self-report from the participants and by interview and clinical evaluation during each visit (every 2 weeks), starting from the day of enrollment until the end of the study (at 6 weeks after enrollment). In addition, participants will be contacted every 2 days via a telephone call, SMS, or other online platform to evaluate any adverse events. A telephone number will be given to all participants to call if there are any suspected abnormalities or any adverse events. Attending obstetricians will assess whether the events are related to the investigational drugs used for GDM. Management will be provided as appropriate by attending obstetricians, and consultation with other specialists will be made as necessary. In case of any adverse events, an additional specific follow-up schedule with related specialists will be offered until they are resolved or considered stable. Assessment of the adverse events and their response to treatment will be by telephone call, self-report, and clinical and laboratory assessment, as appropriate, according to the contexts and nature of the events. All the events will be followed up on until the conditions resolve. All the adverse events will be recorded in detail in the case record form.

In case of withdrawal or termination of the study protocol, such as severe adverse events or noncompliance, treatment will be unblinded. Further individualized management will be provided as appropriate.

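### Controls are given one placebo tablet with no step-up while metformin PR rises to two, so tablet number can reveal the arm from week 4 if the text is followed

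*Protocol article*

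**What the plan says.** The Interventions section of the protocol article sets out the metformin PR arm tablet by tablet. It begins "starting with 750 mg daily (1 tablet of metformin PR 750 mg", moves to one 1000 mg tablet, and then "2 tablets of metformin PR 750 mg will be used for a dosage of 1500 mg per day"; the top level of 2000 mg is two 1000 mg tablets. The control regimen is a single sentence: "Pregnant women who are in the control group will receive 1 tablet of a placebo", followed only by the visit schedule.

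Elsewhere, dose adjustment is not limited to one arm. The Abstract (Methods) mentions 2-weekly adjustment straight after naming both groups. Study Design says: "Each participant will be followed up every 2 weeks for glycemic control evaluation and dosage adjustment for 6 weeks". Blinding says: "All caring obstetricians will be blinded to the treatment and make decisions on dosage adjustment or initiation of insulin therapy at their discretion". On the placebo itself, Blinding says: "Placebos will be prepared by a pharmacist to resemble metformin PR in shape, size, and color". It does not mention the number of tablets.

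**The concern.** A blinded obstetrician who decides to step up a control woman has no defined placebo step to give her. Adjusting the dose only in metformin women would require knowing who they are. The control sentence and the adjustment sentences therefore cannot all be carried out as written.

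If the control sentence prevails, only metformin women ever take two tablets. Each woman knows her own tablet number, and pills are counted at every visit. Three assessments depend on judgment or self-report and are therefore exposed:

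- **Side effects**, a listed secondary outcome: "Side effects will be evaluated by interviewing the participants at each visit".
- **Causality of adverse events**: "Attending obstetricians will assess whether the events are related to the investigational drugs used for GDM".
- **Insulin starts**, whose rate is a listed secondary outcome and which Blinding leaves to the obstetrician's discretion.

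The primary outcome is a glucose threshold assessed by investigators who do not know the arm, so it is less exposed. Strengths and Limitations counts the double-blind design among the trial's strengths, so the text should support it.

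**Working it through.** **Step 1. Tablets per day by dose level (Interventions).** The last column assumes one step per 2-week visit. That is a reading of adjustment at each visit in the listed order, not a stated rule.

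| Level | Metformin PR | Placebo as written | Earliest visit |
|---|---|---|---|
| 750 mg | 1 | 1 | week 0 |
| 1000 mg | 1 | 1 | week 2 |
| 1500 mg | 2 | 1 | week 4 |
| 2000 mg | 2 | 1 | week 6 |

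The arms differ at the two upper levels. On this timing the difference can appear from week 4 to week 6, which is 2 of the 6 treatment weeks and inside the primary outcome window.

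**Step 2. How many women this could involve.** The plan gives no figure on this point. The inputs are its planning values: 40 per group, 20% loss (40 × 0.8 = 32 remaining), and success within 6 weeks of 95% on metformin PR and 70% on placebo.

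The scenario assumes one step per visit for every woman still off target, and no intolerance or withdrawal.

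- Metformin women never at target: 0.05 × 40 = 2 (after loss, 0.05 × 32 = 1.6).
- Metformin successes: 0.95 × 40 = 38. Let f be the share of these that come after week 4.
- Metformin women on two tablets from week 4: 2 + 38f. The document does not give f. At f = 0 the result is 2; at f = 0.10 it is 2 + 3.8 = 5.8; at f = 0.50 it is 2 + 19 = 21.

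**Step 3. Control women.** At the planning rate, 0.30 × 40 = 12 (after loss, 0.30 × 32 = 9.6) never reach target and would stay on one tablet. One tablet in a woman still off target suggests placebo but does not prove it, because step-up is discretionary. These women are not counted.

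**Step 4. Extra placebo if controls are stepped up too.** One additional tablet a day for weeks 4 to 6 is 1 × 14 = 14 per woman. For the 12 women never at target this is 12 × 14 = 168. If all 40 are stepped up it is 40 × 14 = 560.

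**The case against.** The strongest reply is that sham titration is implied. Three places apply dose adjustment without regard to arm, and a pharmacist prepares placebos to match a product supplied in two strengths. On that view the single placebo tablet is simply the counterpart of the one-tablet start. Dispensing detail could also sit in a fuller protocol or pharmacy manual, and Figure 1 was not visible for this check. This reading is possible, and it is why confidence is only moderate. It is not what is written, however. The language of a starting dose and a step-up appears under the metformin arm alone, and no visible text gives a second placebo tablet. The article states both sides of the conflict, so this is more than a detail left out.

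A second objection concerns size, and it stands. A reader might take 2 of 40 as a minimum. The documents do not support that: adjustment is discretionary, and intolerance or withdrawal could keep a woman on one tablet. Nor is a woman unblinded merely by knowing her own tablet number. She, or her obstetrician, must also know that controls never exceed one tablet, and the visible text does not say who is told this.

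Third, exposure through insulin is limited in time. The Abstract's rule starts insulin when target has not been reached within 6 weeks, which is the end of the affected period. That narrows the exposure but does not remove the discretion described under Blinding.

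**Conclusion.** The concern holds as a conflict in the text with a possible partial loss of blinding. Interventions fixes a one-tablet placebo, while the Abstract, Study Design and Blinding require a dose that blinded obstetricians can adjust in either arm. Followed as written, two tablets identifies metformin to anyone who knows the scheme, at the earliest from week 4 under one step per visit.

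In the scenario above, about 2 of 40 metformin women are affected, plus 3.8 for each tenth of the 38 expected successes that come after week 4. The document supports no firm lower bound, and the size of any bias cannot be computed from it.

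A reader might infer that the whole trial is unblinded, that the primary comparison is compromised, or that the sponsor is known to dispense a fixed placebo. The documents support none of these. The difference is confined to the upper two dose levels, the primary outcome is a threshold assessed blind, and the wording may describe only the starting dose.

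Treatment failure is also defined in metformin terms only, in Interventions and Outcomes. This is a minor wording matter with little effect on results, since the Abstract's 6-week insulin rule covers both arms.

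The text should be corrected. Confidence is moderate.

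**What to change.** State in Interventions that control women receive placebo matched to both the 750 mg and the 1000 mg tablet, and that they move through the same four blinded levels (1, 1, 2 and 2 tablets) on the same glycemic rule as the metformin arm.

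If this sham titration is already in use, correcting the control sentence to say so is enough. If it is not, the cost is:

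- a second matched placebo presentation;
- 14 extra placebo tablets per stepped-up control woman for weeks 4 to 6, at most 560 for 40 women;
- a short amendment during recruitment, which the article reports at 24 of 80 women;
- a second inert tablet a day for some control women.

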**Methods:**

A randomized, double-blind, placebo-controlled clinical trial will be conducted among 80 pregnant women diagnosed with GDM who had inadequate glycemic control at a university hospital in Thailand. The women will be randomized into 2 equal groups, receiving either metformin PR or a placebo in addition to nutritional therapy and behavioral modification. Dosage adjustment will be made every 2 weeks. If the glycemic target is not achieved within 6 weeks, insulin therapy will be initiated. All the participants and the investigators are blinded to the treatment provided. The primary outcome is the rate of achievement of glycemic control, and secondary outcomes are time to achieve glycemic control, rate of insulin therapy, and factors associated with the success of metformin PR use.

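### Treatment failure and the insulin start tied to it are defined by a metformin dose that no placebo participant takes and that is probably first prescribed at the last visit, while other sections give different insulin triggers

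*Protocol article*

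**What the plan says.** Interventions sets the metformin PR arm at 750 mg daily to begin with. On visits it says "Follow-up is scheduled every 2 weeks for 6 weeks", with the dose adjusted at each visit according to glycemic control "in a step-up protocol, that is, 750, 1000, 1500, and 2000 mg". The control arm receives one placebo tablet on the same visit schedule, and no placebo counterpart of the dose steps is described.

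Four places bear on when insulin is started:

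- **Interventions and Outcomes:** "Treatment failure is defined as inadequate glycemic control after 2000 mg of metformin PR", followed in both sections by a statement that insulin is then begun.
- **Abstract, Methods:** "If the glycemic target is not achieved within 6 weeks, insulin therapy will be initiated". This is not limited by arm or by dose.
- **Interventions, end of the 6-week period:** "Either the previous treatment will be continued or a new treatment will be initiated, after consultation with an endocrinologist, as appropriate".
- **Blinding:** obstetricians who do not know the allocation decide on dose changes and on insulin as they see fit.

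Safety Management adds insulin for severe hyperglycemia (fasting glucose of 200 mg/dL or more, or glycated hemoglobin of 10% or more).

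The insulin rate is a named endpoint: "The secondary outcomes include time to achievement of optimal glycemic control, rate of insulin therapy, and rate of side effects". The Introduction makes its comparison between the two groups a secondary objective.

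**The concern.** An endpoint compared between randomized arms needs an event that can occur, and be recognized, in both arms during follow-up. The failure definition is worded by exposure to a dose of the active drug, so it describes only one arm. Even in that arm the dose calendar appears to leave no time to observe it. It stands in Outcomes directly after the list that includes the insulin rate, and it is presented there as the reason insulin is given.

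The Abstract and Blinding sections describe different triggers. If clinicians follow different sections, the number of insulin starts depends partly on which sentence was followed and not only on glycemic control. An analysis plan cannot repair this afterwards, because the rule acts on treatment decisions as they are made.

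**Working it through.** The article gives no planning figure for the insulin rate, so there is none to reproduce. The check lays the dose steps on the visit calendar and then sets the insulin rules side by side.

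**1. Sample size, to see whether it depends on this point.** Inputs, from the sample-size paragraph after Figure 1: 95% v 70%, 80% power, 20% loss, two-sided 0.05 (my reading of 95% confidence). With the unpooled normal approximation,

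n = (1.96 + 0.84)² × (0.95×0.05 + 0.70×0.30) / 0.25² ≈ 32.3 per arm, and 32.3 / 0.8 ≈ 40.4.

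The arcsine version gives 31.3, rounded up to 32, and 32 / 0.8 = 40. The stated 40 per group is reproduced from the primary outcome alone. The failure definition does not enter.

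**2. Dose calendar.** There are four levels, hence three step-ups, and visits at weeks 2, 4 and 6.

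| Assumption | Week 0 | Week 2 | Week 4 | Week 6 | First assessment on 2000 mg |
|---|---|---|---|---|---|
| One level per visit | 750 | 1000 | 1500 | 2000 | Week 8, after the study |
| Two levels per visit allowed | 750 | 1500 | 2000 | 2000 | Week 6 |

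To be assessed on 2000 mg at week 6, a woman must make three step-ups over two visits (weeks 2 and 4), so she must move two levels at least once. No section provides for that and none forbids it.

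**3. Placebo arm.** No one in this arm takes 2000 mg of metformin PR. The defined event cannot occur there, whatever is assumed about the calendar.

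**4. One woman, read under each section.** Take a metformin participant not at target at week 6 and on 1500 mg.

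| Section followed | Result |
|---|---|
| Abstract | Insulin is started |
| Failure definition (Interventions, Outcomes) | Not a treatment failure; the insulin start tied to it is not triggered |
| End-of-period sentence (Interventions) | Previous or new treatment, after consultation |
| Blinding | At the obstetrician's discretion |

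A placebo participant not at target at week 6 meets the same split: insulin under the Abstract, never a failure under the definition, discretion under Blinding.

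**5. How many women this concerns.** At one level per visit, every metformin participant uncontrolled at week 6 has been assessed on 1500 mg at most, so this is not a rare case. At the planning rates with 40 per arm, those not at target number 40 × 0.05 = 2 and 40 × 0.30 = 12, or 14 of 80. With 32 per arm after 20% loss they number 1.6 and 9.6, or about 11 of 64. These are counts of women to whom the conflicting sections apply. They do not measure the change in the insulin rate.

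**The case against.** The other side has a substantial case, and it limits the point in several ways.

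- **Countability.** Treatment failure is not itself a listed outcome. The insulin rate is a count of women started on insulin and can be recorded in both arms. A reader might infer that it is undefined under placebo, or that the arms are managed under different rules. The documents do not support that: Blinding describes one blinded decision process for everyone, and the Abstract's rule taken alone treats the arms alike.
- **Magnitude.** A reader might set the Abstract's rule (5% v 30% on insulin at the planning rates) against no insulin at all under the 2000 mg rule, and conclude that the result can swing by 25 percentage points. That treats failure on 2000 mg as the only route to insulin. The text makes it one route, and other sections give others.
- **Timing.** One level per visit is the natural reading of a listed step sequence, but it is not stated, and Blinding allows discretion over dose. The claim that failure can never be observed in the metformin arm is too strong.
- **Risk factors.** A reader might infer that the aim of identifying women at risk of failure has no cases to study. The stated objective concerns factors for success, and non-success is the observable complement of the primary outcome.
- **Other passages.** The end-of-period sentence can mean continue if controlled and change if not, which fits the Abstract. The severe-hyperglycemia threshold is an added safety rule, not a contradiction. The call for longer follow-up under Strengths and Limitations concerns later pregnancy and does not bear on this definition.

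What survives is narrower. The definition cannot describe a placebo participant, it probably cannot be observed by week 6 under metformin, and its insulin trigger differs from those in the Abstract and Blinding. These are conflicts in stated text, not detail that an article leaves to a fuller document.

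**Conclusion.** The point holds for a secondary outcome, with moderate severity. That no placebo participant can meet the failure definition follows from its wording and needs no assumption. That it cannot be assessed within 6 weeks under metformin rests on one dose level per 2-weekly visit. The inconsistency of the insulin triggers rests on the stated text of the Abstract, Interventions, Outcomes and Blinding.

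At the planning rates, roughly 11 to 14 women would be uncontrolled at week 6 and so fall under the conflicting sections. How far this would move the insulin rates or their difference cannot be derived from the documents, because it depends on which section clinicians follow. The primary outcome, its test and the sample size do not use the failure definition and are unaffected.

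**What to change.** 1. Reconcile the Abstract, Interventions, Outcomes and Blinding so that they state the same basis for starting insulin. The content of that rule is a clinical decision for the investigators; no dose, threshold or clinical rule is proposed here.
2. For the analysis, define treatment failure without reference to arm or dose, so that it can be scored in both arms within follow-up. One example is the primary target not met at the primary assessment, or insulin started before it.
3. Count insulin starts over one stated window, identical in both arms, and say whether a start decided at the week-6 visit is included. Record the date and reason of each start, so that starts for severe hyperglycemia can be separated from those for target not met.

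The cost is amendment wording and, if not already collected, one case-report entry for date and reason. The article reports 24 of the planned 80 women as having agreed to take part, so a prompt change would cover most of the sample. For women already treated, the reason for any insulin start can be sought in the medical record.

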### Assignment of Interventions

#### Randomization

Participants will be allocated to receive either metformin PR or a placebo by simple randomization. Central randomization will be used to minimize the risk of bias. The investigator will contact an independent individual to obtain the randomization list at the time of enrollment of each participant.

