### Statistical Methods

Descriptive statistics, including number, percentage, mean, and SD, will be used to describe variables as appropriate. Comparisons of variables between groups will be made using the 2-tailed Student *t* test for continuous variables, such as age, BMI, and gestational age, or the chi-square test for categorical variables, such as parity and GDM risk factors. Comparison of rates of achievement of optimal glycemic control between groups will be performed using the chi-square test. Relative risks and 95% CIs will be evaluated. Time to achieve glycemic control will be compared between groups, using the Student *t* test or Mann-Whitney *U* test, depending on the distribution of the variables. Kaplan Meier curves will be used to estimate the survival curve of time to achieve glycemic control after treatment, and the log-rank test will be used to compare the survival curves between treatment and control groups. Rates of insulin therapy and side effects will be compared using appropriate statistical tests. Missing values will be handled using multiple imputation methods, as appropriate. Subgroup analysis by BMI categories, parity, or GDM risks will be performed as appropriate. All analyses will be performed on an intention-to-treat basis. A *P* value of <.05 is considered to indicate statistical significance.

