### Oversight and Monitoring

#### Safety Management

All participants will receive standard antenatal care at every visit by obstetricians. In addition to physical examination, obstetric examination will be performed, including evaluation of fetal growth and fetal heart rate activity, either by clinical or ultrasonographic examinations. Additional procedures will be provided as appropriate, such as electronic fetal monitoring, detailed ultrasonographic examination, etc.

Glycemic control will be evaluated by FPG and 2-hour PPG or percentage of abnormal SMBG test results. Individual nutritional and behavioral counseling will be provided, customized for each participant. According to institutional guidelines, participants with FPG ≥200 mg/dL or glycated hemoglobin ≥10% will be admitted for further evaluation and initiation of insulin therapy by an endocrinologist.

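### Removing randomized women when an exclusion condition is detected after enrollment contradicts the intention-to-treat rule and can bias the comparison in either direction

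*Protocol article*

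**What the plan says.** Three statements in the protocol article bear on who is analyzed.

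- **Interventions**, last paragraph. The trigger is "If any of the conditions in the exclusion criteria are detected after enrollment, such as congenital anomalies". The consequence is that the allocation is revealed and the woman is "considered as a dropout, and these participants will not be included in the analysis".
- **Randomization.** The investigator contacts an independent person to "obtain the randomization list at the time of enrollment of each participant". Enrollment and allocation therefore coincide, and detection after enrollment means detection after randomization.
- **Statistical Methods.** "All analyses will be performed on an intention-to-treat basis". The same paragraph adds: "Missing values will be handled using multiple imputation methods, as appropriate".

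The exclusion list (Textbox 1, Eligibility Criteria) covers definite or suspected pregestational diabetes, fetal anomaly or death, suspected growth restriction, current glucose-lowering treatment, and contraindication to metformin. Nothing in the article separates conditions that existed before randomization from those that arise or are first suspected afterwards, and nothing reconciles the removal rule with intention-to-treat.

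**The concern.** The two rules define different analysis sets, and both cannot be followed. Under intention-to-treat, a woman found to have an exclusion condition at week 3 is analyzed in her arm, with imputation if her outcome is missing. Under the Interventions rule she disappears, and the missing-data method never reaches her.

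The choice matters because detection of some of these conditions may depend on how the woman is doing on treatment. If so, the women left in each arm are no longer those whom randomization made comparable. The denominator of the primary outcome would then rest on clinical suspicions formed after treatment began. With 80 women planned, a few such removals can change the result.

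**Working it through.** **1. The plan's own figure.** Inputs from the sample-size paragraph: 95% v 70%, 95% confidence (taken as two-sided 5%), 80% power, 20% loss.

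- Arcsine formula: h = 2·asin(√0.95) − 2·asin(√0.70) = 0.708; n = 2·((1.960 + 0.842)/h)² = 31.3, rounded up to 32; 32/0.8 = 40 per group.
- Unpooled-variance formula: n = (0.95·0.05 + 0.70·0.30)·(1.960 + 0.842)²/0.25² = 32.3; 32.3/0.8 = 40.4.

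The stated 40 per group reproduces and is not at issue. The 20% allowance protects numbers (40 × 0.8 = 32 per arm). It does nothing against selective removal.

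**2. Which conditions could be selective.**

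| Condition | Can it first be detected in the 6 weeks? | Possible link to outcome or arm |
|---|---|---|
| Fetal anomaly (the rule's only example) | Yes, but normally present before randomization | None expected |
| Suspected pregestational diabetes | Yes | Marked hyperglycemia on trial may raise the suspicion, so linked to outcome |
| Suspected growth restriction | Yes | Possibly arm; Textbox 1 itself ties it to caution with metformin |
| Contraindication to metformin | Yes | Possibly arm or outcome |
| Fetal death | Yes | Not derivable; week-6 glucose in pregnancy may not exist |

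Pregestational diabetes by definition predates the trial, yet what brings it to light may be the woman's glucose values on treatment. Limiting removal to pre-existing conditions is therefore not enough. The evidence for the condition must also predate randomization.

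**3. Illustration of size.** The number removed is an assumption, because the article gives no frequency. At the planning rates with 40 per arm, expected successes are 0.95 × 40 = 38 and 0.70 × 40 = 28, so expected failures are 2 and 12. The test is the Pearson chi-square without continuity correction, X² = N(ad − bc)²/(product of the four margins). With everyone kept, X² = 80·(38·12 − 2·28)²/(40·40·66·14) = 8.66.

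| Placebo failures removed | Metformin PR | Placebo | Relative risk | X² | p |
|---|---|---|---|---|---|
| 0 | 38/40 (95%) | 28/40 (70%) | 1.36 | 8.66 | 0.003 |
| 2 | 38/40 (95%) | 28/38 (74%) | 1.29 | 6.80 | 0.009 |
| 4 | 38/40 (95%) | 28/36 (78%) | 1.22 | 4.92 | 0.027 |
| 6 | 38/40 (95%) | 28/34 (82%) | 1.15 | 3.05 | 0.081 |

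**4. The other direction.** Suppose both arms truly achieve 70% (28/40 each). Removing 2 failures from the metformin arm only gives 28/38 = 73.7% v 70.0%, an apparent 3.7-point benefit where there is none. If a quarter of metformin-arm failures were removed, a simulation of 200,000 trials with 40 per arm gave a two-sided rejection rate of 8.6%, against 4.8% with nobody removed. The quarter is again an assumption.

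**5. The lower end.** Removals unrelated to outcome and arm, as expected for fetal anomalies, would not be expected to shift either rate. They would only cost numbers.

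**The case against.** The strongest defense is that this is an ordinary late-ineligibility rule. It speaks of conditions detected, not developed, and its one example normally predates randomization and has nothing to do with glucose. Detection comes before unblinding, and the treating obstetricians and assessors are blinded, so knowledge of the arm does not drive who is removed. Blinded exclusion of women who were ineligible from the start can be defended.

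Much of this stands. Unblinding of a woman who is already being removed adds little analytic bias, and any link to arm needs a real drug effect that the article does not quantify. But the rule covers any listed condition with no limit on timing. Blinding to arm is also not blinding to outcome, since the clinicians who form the suspicion have seen the glucose results.

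A reader might infer something stronger: that women put on insulin for poor control leave the denominator because they now use another antihyperglycemic. The article does not support this.

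- The criterion describes status at screening. Applied after randomization, it would also remove the whole metformin arm and would empty the secondary outcome of insulin therapy rate.
- The Abstract, Interventions and Outcomes sections treat insulin as the planned response to failure.
- With a start at 750 mg and one step every 2 weeks through 1000 and 1500 mg, 2000 mg is not reached before week 6. Insulin for treatment failure as defined therefore comes at or after the primary assessment.
- Earlier insulin is possible where obstetricians "make decisions on dosage adjustment or initiation of insulin therapy at their discretion" or under Safety Management, where "participants with FPG ≥200 mg/dL or glycated hemoglobin ≥10% will be admitted for further evaluation and initiation of insulin therapy by an endocrinologist". No frequency is given for either.

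**Conclusion.** The contradiction between the Interventions and Statistical Methods sections is explicit and needs no calculation. It is wrong as written, not a detail left to an analysis plan that is not shown, because the article states both rules.

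That the removals can bias the comparison is a sound inference for suspected pregestational diabetes, suspected growth restriction and a contraindication to metformin. The direction is open and the size cannot be derived. The p values of 0.009, 0.027 and 0.081 rest on the planning rates, 40 analyzable women per arm before removal, and an assumed 2, 4 or 6 placebo failures removed with none from metformin. They show how sensitive a trial of this size is. They do not forecast what will happen, and they do not show that the rule deletes a large share of treatment failures.

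**What to change.** - **Interventions.** Delete the clause that leaves these women out of the analysis. Unblinding and clinical management for safety are unaffected.
- **Statistical Methods.** State that the primary analysis includes every randomized woman in her assigned arm. Collect glycemic data to week 6 where possible, including after study treatment stops. Where that is not possible, for example after a fetal death, apply the missing-data method already planned.
- **Any remaining exclusion.** Limit it to ineligibility shown by facts that predate randomization, judged by someone blind to arm and outcome, and preferably use it only in a sensitivity analysis.
- **Insulin.** Add a sentence that insulin started during the trial is an outcome and not a ground for removal, which closes off the misreading of the current-treatment criterion.

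The cost is a few sentences of protocol wording, the matching text in any analysis plan, and some extra glucose records for women who stop treatment. The Results section expects recruitment to run until September 2026, so the change can be made before the analysis.
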